#### Sample Size and Power

We calculated the sample size requirements to be able to detect a difference between the two arms on our primary outcome measure: the daily parent report of the child’s ER throughout the day. On the basis of the data from our preliminary studies, we expect to see a medium effect size for this measure; therefore, to be conservative, we used a Cohen *d* of 0.3 in our sample size calculation. With this assumption, we calculated the sample size to be able to detect the main effect of the condition (Purrble vs active control) with 90% power and an α level of .05. Under the conservative assumption that the correlation between repeated measures will be 0.75, the required sample size is 92 participants. We inflated this number by 10% to help power the exploratory analyses of the secondary outcomes. Assuming a 20% dropout rate, our final sample size is 120 families.

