Deployments with the research prototypes underpinning the current Purrble [31,32] show that, across all 25 families, children reported that the smart toy was incorporated into the children’s ER practices and engaged with naturally in moments the children wanted to relax or calm down. Specifically, the data from [31] shows that the children interacted with the toy throughout the week-long deployment (eg, average active use for 74.9, SD 64.1 minutes per day; median 60.5), they found the experience enjoyable, and all children requested to keep the toy longer. Children’s emotional connection to the toy appears to have driven this strong engagement. Parents reported satisfaction with and acceptability of the toy. No quantitative data on changes in ER were collected in previous studies because of the small sample size and the focus on feasibility and understanding of appropriation within families.

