### Outcome Measures

The primary outcome will be a daily EMA measure of child emotion regulation capability (as reported by parents) over a period of 4 weeks. Exploratory analyses will investigate the intervention impact on secondary outcomes of child emotion regulation, collected weekly over the same 4-week period, with follow-ups at 1 month and 6 months postdeployment. See Table 1 for a summary of the outcome measures and assessment times.

**Table 1 table1:** Summary of the outcome measures and assessment times.

Outcome measure	Baseline	Deployment				Follow-up			
		Week 1	Week 2	Week 3	Week 4	1 week	2 weeks	1 month	6 months
Perceived child ER ability		Collected daily	Collected daily	Collected daily	Collected daily				
Daily parent report ecological momentary assessment (modified differential emotions scale)		Collected daily	Collected daily	Collected daily	Collected daily				
Daily parent report ecological momentary assessment (engagement)		Collected daily	Collected daily	Collected daily	Collected daily				
Daily parent report ecological momentary assessment (reaction to triggers)		Collected daily	Collected daily	Collected daily	Collected daily				
Weekly parent questionnaire (Strength and Difficulties Questionnaire)	✓	✓	✓	✓	✓			✓	✓
Weekly parent questionnaire (ER Checklist)	✓	✓	✓	✓	✓			✓	✓
Weekly parent questionnaire (Twente Engagement With eHealth Technologies Scale)		✓	✓	✓	✓			✓	✓
Weekly children questionnaire (Difficulties in ER Scale)	✓	✓	✓	✓	✓			✓	✓
Weekly children questionnaire (emotion regulation-beliefs)	✓	✓	✓	✓	✓			✓	✓
Interviews with families						✓	✓		

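### The design described does not deliver the stated 90% power at 92 participants for d = 0.3, unless baseline SDQ correlates about 0.75 with each daily score

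*Protocol article*

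**What the plan says.** Under Sample Size and Power, the article sizes the trial "to be able to detect the main effect of the condition (Purrble vs active control") on the daily parent report. It states "we used a Cohen *d* of 0.3 in our sample size calculation", "with 90% power and an α level of .05", and then: "Under the conservative assumption that the correlation between repeated measures will be 0.75, the required sample size is 92 participants". It adds 10% for secondary outcomes and allows for 20% dropout, ending at 120 families. The abstract gives 134. The paragraph does not name the formula, the number of repeated measures or the sidedness.

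The source given for the effect size is: "On the basis of the data from our preliminary studies, we expect to see a medium effect size for this measure". The Intervention section (Purrble—Intervention Design and Logic Model) says: "No quantitative data on changes in ER were collected in previous studies".

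Under Outcome Measures, the article states: "The primary outcome will be a daily EMA measure of child emotion regulation capability (as reported by parents) over a period of 4 weeks". In Table 1 the row "Perceived child ER ability" has entries for deployment weeks 1 to 4 only, and its Baseline cell is empty. The SDQ row does have a baseline. Under Data Analyses, the models carry a random intercept and a random slope for time and adjust for the baseline SDQ total difficulties score.

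**The concern.** For a comparison of arms averaged over repeated scores, a correlation of 0.75 means that 28 days carry little more information than one. A small standardised difference then needs several hundred families. A figure of 92 implies a large gain in precision from somewhere, so the question is whether the planned analysis can supply it.

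At stake is how the primary result will be read. If 90% power is taken at face value, a non-significant result looks like good evidence against an effect of 0.3. If the true power is well below 90%, it is much weaker evidence. The article also plans to use these data to size later studies, so the basis of this calculation should be clear.

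**Working it through.** **Inputs.** d = 0.3, 90% power, α = .05 and correlation ρ = 0.75 come from Sample Size and Power. The number of measures, m = 28, follows from daily collection over 4 weeks. Allocation with probability .5 comes from the abstract. I assume a two-sided test, compound symmetry, d in units of the single-day SD, and complete data. (1.96 + 1.2816)² = 10.51.

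**Reproducing 92.**

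- *Route A: ANCOVA with a baseline of the same measure.* The variance factor is (1 + 27 × 0.75)/28 − 0.75² = 0.7589 − 0.5625 = 0.1964. N per arm = 2 × 10.51 × 0.1964/0.09 = 45.9, so 46 per arm and 92 in total.
- *Route B: between-factor F test with Cohen's f = 0.3.* The noncentrality is 0.09 × 92 × 28/(1 + 27 × 0.75) = 10.91. On 1 and 90 degrees of freedom the power is 0.9045. For two equal groups d = 2f, so this corresponds to d = 0.6, not 0.3.

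The article does not show which route was used.

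**Does the design supply what Route A needs?** Route A needs a pre-toy score on the daily measure. Table 1 has none. The covariate in the model is baseline SDQ, and the stated 0.75 is a correlation between repeated measures, not between the SDQ and a daily score.

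**Power with the planned covariate.** Let r be the correlation of baseline SDQ with a daily score. The article does not give it, so it is an assumption. The variance factor is v = 0.7589 − r². Power comes from the noncentral t distribution with noncentrality 0.3/√(4v/N). For example, at r = 0 and N = 92 the noncentrality is 0.3/√(4 × 0.7589/92) = 1.65, and power is 37%.

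| r | v | N = 92 | N = 120 | N = 134 |
|---|---|---|---|---|
| 0 | 0.7589 | 37% | 47% | 51% |
| 0.3 | 0.6689 | 41% | 51% | 56% |
| 0.5 | 0.5089 | 51% | 63% | 68% |
| 0.7 | 0.2689 | 78% | 88% | 91% |
| 0.75 | 0.1964 | 90% | 96% | 97% |

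A simulation of 20,000 trials at N = 92 gave 37.8% with no covariate and 89.5% with a same-measure baseline.

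**What r = 0.75 would mean.** Baseline SDQ would have to explain 0.5625/0.7589 = 74% of the variance of the 28-day mean.

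**With no covariate gain (r = 0).** The total N for 90% power is 4 × 10.51 × 0.7589/0.09, about 354. The d detectable with 90% power is 3.2415 × √(4 × 0.7589/N), which is 0.59 at N = 92 and 0.49 at N = 134.

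**Is 0.75 conservative?** Under Route A the total N is 4 × 10.51 × [(1 + 27ρ)/28 − ρ²]/0.09. This gives about 110 at ρ = 0.3, 125 at 0.5, 103 at 0.7 and 92 at 0.75. The requirement peaks near 0.5, so 0.75 is a favourable choice there. In a between-arm test with no baseline, N does rise with ρ and the label would fit, but that test does not give 92 at d = 0.3.

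**Effect-size source.** One section bases the expected medium effect on preliminary data. Another says that earlier studies collected no quantitative data on change in emotion regulation. The abstract and Introduction likewise say that quantitative evidence on child outcomes is lacking.

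**The case against.** The strongest reply is that 92 is not an arithmetic slip. A standard baseline-adjusted formula returns it exactly from the stated d, correlation, α and power, and the planned model is baseline-adjusted. This stands as far as the sum goes. What fails is the match between the formula and the design, because the adjustment is for a different instrument. Recruitment also restricts SDQ to scores of 10 or more, which would tend to weaken its correlation with the daily scores.

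A reader might infer that the trial's power is 37%. The article does not support that. The 37% assumes that SDQ adjustment gains nothing, whereas the article includes it to reduce noise. With no correlation given, only a range can be stated.

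A reader might also infer that the trial would miss d = 0.3 more often than it would find it. That is not established either. Power is about 51% at N = 134 even with r = 0, and passes 50% at N = 92 by r = 0.5. Treating all dropouts' data as lost would be too pessimistic, since the intent-to-treat mixed model keeps the days they supplied. In the other direction, missed days and the random slope would generally lower power below the table.

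Nor can it be said that f was entered for d, or that Route A is the only match. A one-sided ANCOVA with 5 follow-ups has factor (1 + 4 × 0.75)/5 − 0.5625 = 0.2375 and also gives 92 (45.2 per arm). It does not fit daily collection, and it too needs a same-measure baseline.

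Finally, the trial is called exploratory and promises cautious conclusions. This limits the harm, but it does not make the stated 90% correct.

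**Conclusion.** The point holds in this form: the stated 90% power for d = 0.3 at 92 participants is not delivered by the design in the article unless baseline SDQ correlates about 0.75 with each daily score, and nothing in the article supports that. For r from 0 to 0.7, power is about 37% to 78% at N = 92, 47% to 88% at N = 120 and 51% to 91% at N = 134. At 134, then, 90% is reachable, but only with a correlation near 0.7. These figures rest on 28 measures, compound symmetry, a two-sided .05 test and complete data.

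Two smaller faults go with it. The *conservative* label on 0.75 is wrong under the ANCOVA formula that yields 92. The preliminary-data source for the effect size is contradicted by the article's own account of the earlier studies. That contradiction needs no calculation.

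**What to change.** Restate the Sample Size and Power paragraph, without asking for more families:

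- Name the formula, the sidedness, the number of repeated measures and the assumed correlation between baseline SDQ and the daily score.
- Replace the single 90% with power for d = 0.3, or the d detectable with 90% power, over a stated range of that correlation at the planned sample size. State the assumptions about missing data beside it.
- Drop *conservative* and the attribution to preliminary data, and call d = 0.3 an assumption.

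The Results section reports that primary data collection ended by mid-May 2021, so what can change is the statement and not the assessment schedule. The cost is rewording one paragraph and accepting a less favourable stated power.

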**Methods:**

Overall, 134 children aged 8 to 10 years will be selected from an *enriched* nonclinical North American population; for inclusion, the cutoff for the parents’ rating of child dysregulation will be ≥10 points in the total difficulties score on the Strengths and Difficulties Questionnaire. This cutoff was selected to obtain a measurable, but not necessarily clinical, level of the child’s emotion regulatory difficulties. The selected families will be randomly assigned with .5 probability to receive either a Purrble or an active control (noninteractive plush toy). The primary outcome will be a daily ecological momentary assessment measure of child emotion regulation capability (as reported by parents) over a period of 4 weeks. Exploratory analyses will investigate the intervention impact on secondary outcomes of child emotion regulation, collected weekly over the same 4-week period, with follow-ups at 1 month and 6 months postdeployment. Quantitative data will be analyzed on an intent-to-treat basis. A proportion of families (approximately 30% of the sample) will be interviewed after deployment as part of the process analysis.

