#### Postdeployment Interviews (Process Analysis)

We will collect semistructured interview data with parents of up to 40% of the experimental group sample (20-25 families), and approximately 25% of the control group (15 families). The interviews will be conducted within 2 weeks following the primary data collection period. We will specifically aim to recruit families who show the highest or lowest change in the outcome data over the primary period to qualitatively understand the potential moderators of intervention responses for future research.

Following previous work [31], the semistructured interview guide will explore the engagement with the toy, any qualitative changes in child or family behavioral patterns that parents notice, appropriation (ie, how the intervention ended up being used by different participants), and use trajectory over time. In addition, we draw on the data from daily questionnaires as part of the interviews, such as discussing the trajectories of daily parental reports on child ER with the parent (eg, asking about specific instances where there is a spike or as a way of referring to particular times in the deployment).

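### The planned sample size is given as both 134 and 120, and neither follows from the stated 10% and 20% inflation steps when dropout is allowed for properly

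*Protocol article*

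**What the plan says.** The Methods paragraph of the abstract in the protocol article gives the target as follows: "Overall, 134 children aged 8 to 10 years will be selected". The same paragraph goes on to say that the selected families are randomised with probability one half, so 134 reads as the number to be randomised.

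The section Sample Size and Power builds its figure in three steps. For the primary outcome, "the required sample size is 92 participants". Then: "We inflated this number by 10% to help power the exploratory analyses of the secondary outcomes". Finally: "Assuming a 20% dropout rate, our final sample size is 120 families".

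The section Postdeployment Interviews plans 20 to 25 interviews in the experimental arm, capped at 40% of that arm, and for the controls "approximately 25% of the control group (15 families"). The abstract puts interviews at about 30% of the whole sample.

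**The concern.** The planned sample size is a core prespecified quantity, and here it appears twice with different values. A reader comparing achieved enrolment with the plan cannot tell whether the trial met, missed or exceeded its target.

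There is also an arithmetic question. A sample inflated for dropout should, once that dropout occurs, leave the number it was inflated from. If 120 does not leave about 101 families after 20% dropout, the margin announced for the secondary outcomes is not delivered.

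**Working it through.** **Inputs** (Sample Size and Power, except the last): base 92; inflation 10%; dropout 20%; final figure 120. Abstract: 134.

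**Trying to reproduce 120**
- Add both percentages on the base: 92 x (1 + 0.10 + 0.20) = 119.6, so 120. This matches.
- Multiply in sequence: 92 x 1.10 x 1.20 = 121.4, so 122. This is close.
- Omit the 10% step: 92 / 0.80 = 115. No match.

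**The stated steps with dropout allowed for as n / (1 - dropout)**
- 92 x 1.10 = 101.2
- 101.2 / (1 - 0.20) = 126.5, so 127
- With equal arms: 46 x 1.10 = 50.6 per arm; 50.6 / 0.80 = 63.25, so 64 per arm and 128 in total

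**Trying to reproduce 134.** None of the combinations above gives it. Dividing by both complements also fails: 92 / 0.90 / 0.80 = 127.8.

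**What each total leaves after 20% dropout**

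| Randomised | Remaining | Margin over 92 |
|---|---|---|
| 120 | 120 x 0.80 = 96 | 4 / 92 = 4% |
| 127 | 127 x 0.80 = 101.6 | 9.6 / 92 = 10% |
| 134 | 134 x 0.80 = 107.2 | 15.2 / 92 = 17% |

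**Dropout implied if 101.2 are to remain**
- From 120: 1 - 101.2 / 120 = 15.7%
- From 134: 1 - 101.2 / 134 = 24.5%

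**Whether the interview numbers identify the total** (60 per arm under 120, 67 per arm under 134)
- Control arm: 15 / 60 = 25%; 15 / 67 = 22.4%, still roughly a quarter
- Experimental arm, upper end: 25 / 60 = 41.7%, above the 40% cap; 25 / 67 = 37.3%, within it
- Whole sample, 35 to 40 interviews: 29% to 33% of 120; 26% to 30% of 134

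The control-arm fraction leans to 120 and the experimental-arm cap leans slightly to 134. Both totals fit roughly.

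**The case against.** The best defence is that 120 has a source and does little harm. Adding the percentages on the base gives it almost exactly, so it is a non-standard dropout allowance and not an arbitrary number. The requirement for the primary outcome is 92, and 96 exceeds it. The 10% was added only for exploratory outcomes, in a trial that calls itself exploratory and sets no power target for them. The Data Analyses section uses all randomised participants in random-effects models, so families who drop out still contribute the days they reported, and counting completers overstates the information lost. All of this stands, and it limits the consequence. It does not make 120 the result of allowing for a 20% dropout rate, and it does not explain 134.

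Four stronger readings are tempting, and the article does not support them.

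- **That this error leaves the primary analysis short.** On the article's own figures it does not, because 96 is above 92. Whether 92 itself follows from the stated effect size of 0.3 is a separate question. Here it is taken as given, and nothing here shows that any of these totals secures 90% power.
- **That the interview plan proves 120 to be the working target.** The fractions do not separate 60 from 67 per arm.
- **That recruitment had no clear stopping point.** The Results section reports that primary data collection had finished by mid-May 2021. What remains is an unclear record of the plan.
- **That 134 is a screening count and 120 the number randomised.** The abstract says that the selected families are the ones randomised, and 120 already includes the dropout allowance.

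**Conclusion.** The point holds in two parts. The firmer part is the contradiction: 134 in the abstract and 120 in the sample-size section, 14 families apart (14 / 120 = 12%), with no reconciliation. The second part is arithmetic: with a proper dropout allowance the stated steps give 127, or 128 for equal arms, which is neither published figure.

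At 120, the stated dropout leaves 96 families, about 5 fewer than the 101.2 from which the paragraph started (101.2 - 96 = 5.2), so the 10% margin falls to 4%. The loss touches only the margin for the exploratory secondary outcomes. At 134 there is no shortfall, but the figure has no stated derivation.

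This rests on taking 92, 10% and 20% as stated, and on reading a 20% dropout rate as one fifth of randomised families lost.

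**What to change.** State one target in both the abstract and Sample Size and Power, and show each step, using n / (1 - dropout) for the dropout allowance.

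- If the stated steps are kept, the figure is 127, or 128 for equal arms.
- If the target is 120, say that it leaves 96 families after 20% dropout, a 4% margin over 92.
- If the target is 134, give the assumption that produces it. Starting from 101.2, it implies about 24.5% dropout.
- If the target changed from one figure to the other, say so and give the date.

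The interview fractions need no correction on this ground. The cost is a few sentences of text; design, data collection and analysis are unaffected.

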### Ethical Criteria and Ethics Committee

The study will be conducted according to local regulations and the Declaration of Helsinki. The Pearl institutional review board approved the study (#18-CFC-101). Written informed consent will be obtained from all parents, and written assent will be obtained from all children. The trial is registered with ClinicalTrials.gov (NCT04810455).

## Results

This study is funded by the UKRI Future Leaders Fellowship (MR/T041897/1) and the Committee for Children. The ethical approval was received, and the study is preregistered with ClinicalTrials.gov. The recruitment procedures started in early March 2021. The data collection started in mid-April 2021, with the primary data collection period finished by the mid-May 2021.

## Discussion

### Principal Findings

This study aims to evaluate the benefits of access to a socially assistive robot on children’s ER ability in situ, without the need for training for the child or parents. If successful, the study will provide a proof-of-concept example of a *bottom-up* ER intervention, enabling a new approach to developing child ER competency through technology-enabled ongoing support in everyday emotional situations. As such, this work complements the currently predominant *top-down* approaches, where ER strategies are taught in training contexts, and then the children are expected to transfer these strategies into daily life, often with no or limited in situ support. If shown effective, these in situ interventions can inspire a new approach in how ER interventions can be conceptualized, designed, and delivered.

More generally, ER in childhood is a prime target for a range of prevention and clinical interventions. In this regard, the existing Purrble toys can be seen as a potentially highly modular and extendable platform, where additions or minor changes to the core interaction paradigm can be used to target a range of participants (different ages, verbal acuity, etc), and a variety of different contexts (clinical and nonclinical settings). For example, our pilot data with clinicians and psychotherapists suggest potential benefits in the context of eating disorders and self-harm interventions for adolescents, as well as complementing therapeutic support for fostered or looked-after children. Rigorous empirical data supporting the efficacy of the current intervention are crucial for such research.

### Limitations

The following limitations of this study need to be considered. First, this study is designed as an exploratory RCT to account for the uncertainty about the effect sizes that should be expected given the novelty of the intervention delivery mechanism and proposed theory of change. The range of selected secondary measures (and the substantial qualitative process analysis) reflects this focus on hypothesis generation rather than aiming to design a definitive trial.

Second, a related limitation concerns the choice of primary measure. The bespoke 4-item composite measure of the parent-reported *child emotion regulation* ability throughout the day reflects the uncertainty about the impact of the intervention on distal ER outcomes, aiming to measure time-sensitive proximal aspects of the expected changes in child emotion regulatory ability that are also directly observable by the parent. Future work should target more established measures such as those targeted by the secondary outcome in this study (SDQ, ERC, DERS, and ER beliefs). We expect that the necessary sample size estimation for such studies will be guided by the empirical data collected in this study.

Third, the current commercial Purrble toys lack the capability to track in-the-moment interactions over time or gather any other data on daily use, as do the noninteractive active control units. As such, the study lacks objective measures of daily engagement and needs to rely on observer-report measures (parents), who are unlikely to fully account for the child’s independent use of the toy. In addition, the lack of in-the-moment tracking also limits the methods available to verify level 1 (in-the-moment soothing) and level 2 mechanisms (child-initiated repeated interaction) from the theory of change. If the data from this study show the impact of the Purrble intervention on child ER in situ, future mechanistic or optimization studies should specifically focus on testing the pressumed level 1 and 2 processes.

Finally, the study design relies predominantly on end-of-day parent reports of child ER under naturally occurring daily stressors. This is in line with other studies on similarly aged child samples, and the ecological validity of the findings is a strength of the study design. However, further work could extend these methods with more controlled measures, such as in-laboratory experimental measures, as another triangulation of the meaningful impact of the intervention on child ER.

